### Randomization

Patients will be consecutively and randomly assigned to one of four groups in a 1:1:1:1 ratio. Randomization will occur before the first acupuncture treatment. A computerized random number generator will be used to generate the randomization sequence. Allocation concealment will be performed via sequentially numbered opaque, sealed envelopes by an investigator who is not involved in recruitment or assessment of the results.

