### Outcome measurement

Outcome measurements will be assessed at baseline and after the treatment phase. We will use multiple outcome measurements, including subjective and objective parameters.

The patients will be required to complete several subjective questionnaires before and after treatment, including the following: the Vertebrobasilar System Ischemic Neurological Impairment Scale (VBS-INIS) (range: 0 to 22) [17], UCLA Dizziness Questionnaire (UCLA-DQ) (range: 5 to 25) [18], Activities of Daily Living Scale (ADL) (range: 14 to 56) [19], and Psychological and Social Adaptation Scale (range: 0 to 20) [20]. All scales have been validated in previous studies.

The VBS-INIS assesses the degree of neurological impairment caused by vertebrobasilar ischemia. Common signs and symptoms include dizziness, deafness or tinnitus, double vision, dysarthria, or swallowing impairment. The scale was demonstrated to be uniform, stable, and reliable. Higher scores indicate more severe damage.

The UCLA-DQ is used to measure the severity and frequency of dizziness. The questionnaire contains five items to evaluate the patients in terms of daily activity, quality of life, and their fear of dizziness.

The ADL is a validated questionnaire that has been widely used to assess ability of an individual to function in daily life. The questionnaire consists of two parts: the Physical Self-Maintenance Scale and the Instrumental Activities of Daily Living Scale.

The Psychological and Social Adaptation Scale mainly describes the impact of dizziness on daily life and work. The scale assesses psychological parameters, such as temper, worry, fear, quality of sleep, and communication with others. The reliability, availability, and sensitivity of this scale had been clinically tested [20].

Objective parameters will also be used to compare differences in cerebral blood flow via TCD and carotid ultrasonography. Changes in cerebral oxygenation will be investigated using near-infrared spectroscopy, and the inherent mechanism underlying acupuncture treatment efficacy will be investigated using metabolomics (Figure 2).

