### Statistical analysis

#### Sample size

We estimated the sample size using a formula, as was performed in relevant literature studies. We plan to enroll a total of 144 participants, with 36 individuals in each group, allowing for a 20% withdrawal rate.

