#### Analysis strategy

Statistical analysis will be performed using the statistical software package SPSS 16.0 for Windows (SPSS Inc., Chicago, IL, USA). Differences between the baseline characteristics of each treatment group will be analyzed using an analysis of variance (ANOVA) for continuous variables such as age, body mass index, and disease course. Comparisons among the baseline characteristics of the four groups for categorical variables, such as gender and medical history, will be made using the chi-square test. Paired sample *t*-tests will be used to compare the subjective and objective outcome measurements before and after treatment. Comparisons of the subjective and objective outcome measurements among the four groups will be performed by ANOVA. A *P* value of less than 0.05 will be considered statistically significant. Qualified statisticians will perform the statistical analyses in a blinded manner.

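### The four-group comparison is a plain ANOVA without a baseline covariate, although every outcome is also measured at baseline; ANCOVA would be more precise at almost no cost

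*Protocol article*

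**What the plan says.** The Outcome measurement section sets two assessments: "Outcome measurements will be assessed at baseline and after the treatment phase". This covers the four questionnaires and the blood-flow measures. Cerebral oxygenation is described as a change.

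The Analysis strategy section then names three kinds of test.

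- Baseline characteristics: "Differences between the baseline characteristics of each treatment group will be analyzed using an analysis of variance (ANOVA) for continuous variables", with chi-square tests for categorical ones. The examples are age, body mass index, disease course, gender and medical history.
- Before against after treatment: paired t-tests.
- Between groups, for subjective and objective measures alike: "outcome measurements among the four groups will be performed by ANOVA".

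No covariate is named for the third. The significance level is 0.05. Under Randomization, patients are "randomly assigned to one of four groups in a 1:1:1:1 ratio", with no stratification by baseline severity described. Under Sample size: "We plan to enroll a total of 144 participants, with 36 individuals in each group, allowing for a 20% withdrawal rate". The document gives no effect size, standard deviation, power or baseline-to-post correlation.

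**The concern.** The trial has no sham arm and sets out to compare four active manipulations directly, so the between-group test is the one that answers its question. It is also the only outcome comparison in which the plan gives the baseline score no stated role.

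Two things are at stake. The first is precision: a baseline score usually explains part of the variation in the later score, and an ANOVA of post-treatment values leaves that part in the error term. Differences among four active arms may be modest, and recruitment has closed (Trial status), so precision can no longer be bought with patients. The second is chance imbalance: with about 29 patients per arm, two groups can differ noticeably at baseline by luck, and the planned test does not allow for this if it uses post-treatment values.

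**Working it through.** **Inputs from the document.** Four arms of 36 give 4 × 36 = 144, which matches the stated total. With 20% withdrawal, 36 × 0.8 = 28.8, so about 29 per arm and N = 4 × 29 = 116. Alpha is 0.05. The sample size itself cannot be reproduced, because the formula and its inputs are not given.

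**Assumptions, not in the document.** Correlation r between baseline and post-treatment values of 0.3, 0.5 or 0.7; equal variance at both times; a linear relation. For power, a 0.5 SD difference between the two levels of one factor (direction or frequency) and no effect of the other.

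**Error variance**, in units of the post-treatment variance:

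- ANOVA of post-treatment values: 1
- ANOVA of changes: 2(1 − r)
- ANCOVA: 1 − r²

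The ANCOVA cut is therefore r² against post-treatment values. Against changes it is 1 − (1 − r²)/[2(1 − r)] = (1 − r)/2.

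| r | ANCOVA variance | Cut v post-treatment ANOVA | Cut v change ANOVA |
|---|---|---|---|
| 0.3 | 0.91 | 9% | 35% |
| 0.5 | 0.75 | 25% | 25% |
| 0.7 | 0.51 | 49% | 15% |

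A simulation with 29 per arm gave reductions of 9.0% at r = 0.3 and 49.0% at r = 0.7 in the first comparison.

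**Cost of the covariate.** Estimating one slope multiplies the variance of an adjusted difference by about 1 + 1/(N − 6) = 1 + 1/110 = 1.009, which is under 1%. At r = 0.3 the net variance is 0.91 × 1.009 = 0.918, a cut of 8.2%. At r = 0.7 it is 0.51 × 1.009 = 0.515, a cut of 48.5%.

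**Power of the planned four-group test.** A 0.5 SD effect of one factor puts two group means 0.25 SD above the overall mean and two 0.25 SD below it, so f = 0.25. The noncentrality is N f² = 116 × 0.0625 = 7.25, divided by the error variance above. The F test has 3 and 112 degrees of freedom (111 with the covariate).

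| Analysis | r = 0.3 | r = 0.5 | r = 0.7 |
|---|---|---|---|
| ANOVA, post-treatment | 59% | 59% | 59% |
| ANOVA, change | 44% | 59% | 83% |
| ANCOVA | 63% | 73% | 89% |

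The ANCOVA noncentralities are 7.25/0.91 = 7.97, 7.25/0.75 = 9.67 and 7.25/0.51 = 14.22. The 1.009 factor lowers the ANCOVA power by less than half a percentage point.

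**Chance imbalance.** The standard deviation of the difference between two baseline means is √(2/29) = 0.26 SD. Given a baseline difference of that size, the expected shift in an unadjusted post-treatment comparison is r × 0.26, or 0.08 / 0.13 / 0.18 SD. In a comparison of changes it is (1 − r) × 0.26 in the opposite direction, or 0.18 / 0.13 / 0.08 SD. ANCOVA removes the shift if the linear relation holds.

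**The case against.** **The plan is not in error.** A reader might infer that the unadjusted ANOVA is biased or that its P values are wrong. The document does not support that. Under randomisation the comparison is unbiased over repeated allocations, and its standard error already reflects chance imbalance. What is lost is efficiency, and protection against the particular imbalance that occurs. This objection stands in full and limits the point to a recommendation.

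**Baseline may not be left out.** A reader might infer that baseline values play no part in the comparison. The Analysis strategy section does not say which values enter the ANOVA, and one outcome is itself described as a change. With change scores, baseline enters by subtraction. This stands, which is why both readings are calculated. ANCOVA is more precise on each.

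**The gain could be overstated.** It rests on an assumed correlation. At r = 0.7 the 51% is the variance that remains, not the cut. A single-degree-of-freedom contrast for one factor, with the same inputs, would show power rising from 76% to 96% at r = 0.7, but that is not the four-group test the article plans.

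**A separate analysis plan may specify adjustment.** It may, and model details are often left to it. But the article does more than stay silent: it names the test. A plan with ANCOVA would depart from this text, and the two would need to be reconciled.

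**The baseline significance tests.** A reader might count these as a fault that affects results. They tell little in a randomised trial, but the article makes no analysis decision depend on them, so they change nothing.

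**Conclusion.** The point holds as a loss of efficiency in a valid test. The qualitative conclusion, that ANCOVA is the more precise choice, holds whether the ANOVA uses post-treatment or change values and at every correlation examined. The sizes are conditional: they depend on a correlation, and for power an effect size, that the document does not supply. On the post-treatment reading the gain grows with the correlation; on the change reading it shrinks. Adjustment deals with chance imbalance in the outcome's own baseline score only, not in other prognostic factors.

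**What to change.** In the Analysis strategy section, replace the between-group ANOVA with an ANCOVA: the post-treatment value of each outcome as the response, treatment group as the factor, and that outcome's own baseline value as the covariate. Report adjusted differences between groups with 95% confidence intervals. This also settles which values are compared.

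No new data are needed. The cost is one error degree of freedom per model and an assumed roughly linear baseline relation, which can be checked on a plot because several of the scales are bounded. As recruitment has ended, the change should be dated and fixed before outcomes are compared by group. If that has already happened, it should be reported as made afterwards, beside the planned ANOVA.

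Presenting baseline characteristics descriptively instead of testing them is optional and alters no result.

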## Discussion

Typically, acupuncture manipulations refer to the various manipulations performed by an acupuncturist after the needle is inserted. TCM theory suggests that various styles of acupuncture manipulations are closely associated with different clinical effects. Long-term practices in our hospital (The National Clinical Research Centre of Acupuncture and Moxibustion) also support this theory. Recent studies [9,10,21] have demonstrated that different acupuncture manipulations exert different influences on pain, acupuncture sensation (*de qi*), and blood perfusion. However, few studies have investigated the direct relationship between needle manipulations and clinical outcomes. Therefore, this trial aims to investigate the potential clinical differences that result from diverse manipulations.

Rigid quality control will be used in this trial to reduce potential bias. Experienced subjects might be able to distinguish real acupuncture from sham acupuncture in appearance or sensation [22]. Therefore, sham acupuncture might not be effective in the Chinese population. All groups will receive verum acupuncture, and patients will have their backs turned to the acupuncturist. The subjects will not observe the manipulations conducted by the acupuncturist. Moreover, an inquiry will be performed to investigate whether the subjects were truly blinded to the treatment received.

We selected a pragmatic randomized controlled trial after an extensive discussion. Although both pragmatic and explanatory randomized controlled trials play important roles in the evaluation of health care interventions, the objectives and procedures of the two methods are different [23]. The primary objective of the explanatory trial is to determine whether acupuncture is better than placebo. Explanatory trials are an absolute proof for the validation of a therapeutic intervention [24]. To evaluate complex interventions such as acupuncture, the explanatory randomized controlled trial might not be an appropriate study design [25]. Instead, pragmatic randomized controlled trials can effectively investigate the overall impact of a group of treatments. Pragmatic trials can also provide a real comparison in clinical practice, which can provide a cost-effective analysis and can directly relate to policy. In pragmatic trials, the important question is whether the overall effect is worth the cost [23,26,27]. From a methodological perspective, explanatory RCTs demand rigorously controlled experimental conditions and the use of a placebo control [28]. Using a less rigidly controlled study design than those of explanatory RCTs, pragmatic trials can compare different interventions under actual clinical conditions, and placebo controls are not required [29]. However, pragmatic trials contain inherent deficiencies. Because of differences in needling techniques, treatments often include subtle variations, rendering the trials difficult to replicate [30]. To overcome this flaw, we will use a standardized acupuncture manipulation. The acupuncture treatments will be conducted by one acupuncturist with adequate clinical experience. Before conducting the trial, the acupuncturist received professional training to ensure accurate needle operation. Therefore, this trial should demonstrate adequate reproducibility.

This study is based on the quantity theory of acupuncture manipulation developed by [name]. This method aims to define and quantify acupuncture manipulation. The quantity theory of acupuncture manipulation has rendered the quantification of acupuncture more feasible and has contributed to the standardization, repeatability, and control of acupuncture studies. This method could be used to determine the optimal treatment method based on different parameters.

This study includes some limitations that may affect the results. First, we will not conduct a follow-up study. We consider the observation of the short-term therapeutic clinical effects sufficient to investigate our hypothesis, but our study design is insufficient for evaluating long-term effects. Moreover, the outcome measurement scales may contain bias when translated into Chinese, which could influence the results of the trial. Furthermore, because Chinese patients expect acupuncture to be effective, the placebo effect may exert a stronger influence on the results than if the study is performed with mostly Western patients. To reduce this bias, we will use multiple outcome measurements, including subjective and objective outcome measurements. The placebo effect might significantly influence subjective outcomes but should not significantly affect objective measurements [31]. Finally, we did not use sham acupuncture. Because Chinese patients generally trust acupuncture, informed consent for the use of sham acupuncture is difficult to obtain [32]. A previous study also demonstrated that acupuncture is an effective intervention for PCIV; therefore, we want to compare different acupuncture methods [8].

The results of this study may help explain the contradictory results obtained from acupuncture studies if the different manipulations can induce different treatment effects [33]. This study could also elucidate the overall treatment effect of acupuncture on patients with PCIV. The use of both subjective and objective outcome measurements should allow the identification of significant differences between these two outcome measurements.

In conclusion, this study will attempt to explore the relative efficacies of different acupuncture manipulations and their mechanisms of action. Because the focus of this study is highly specific, the findings may have implications for a number of ongoing debates in the field of acupuncture research.

### Trial status

The trial had finished the recruitment phas in August 2014.We will report the results in later article.

## Abbreviations

ADL: Activities of daily living
CRF: Case report form
DBP: Diastolic blood pressure
ECG: Electrocardiogram
MRI: Magnetic resonance imaging
PCIV: Vertigo resulting from posterior circulation ischemia
SBP: Systolic blood pressure
TCD: Transcranial doppler
UCLA-DQ: University of California, Los Angeles-dizziness questionnaire
VBI: Vertebrobasilar insufficiency
VBS-INIS: Vertebrobasilar system ischemic neurological impairment scale
